### Power calculation

There are no previous studies giving any clear suggestion of the number of high-risk individuals that can be recruited from a well-defined catchment area sample like the current, but previous studies in Melbourne indicate that around 20% of first episode patients have been in contact with the PACE clinic ([name], personal communication). Studies up to now give a conservative estimate of a 20% transition rate over the first two years for a non-treated high-risk sample and subsequently a 10% risk in the active treatment group. A power analysis has shown that in order to give an achieved significant reduction of transition rates in the study population with the proposed sample size for the two groups of a) 750 000 with predicted annually detection of 150 first-episode psychosis (FEP) (Bergen and Østfold) and b) 440 000 with annually predicted reduction to 90 FEP (Stavanger and Fonna) through prodromal detection and intervention, the study will have power of 88.9% to yield a statistically significant result.

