### Prodromal inclusion and exclusion criteria

Start of study inclusion is from March 1^st^ 2012, ending inclusion December 31^st^ 2016.

1) The patient is listed in the national register and residing in the catchment areas of: Stavanger and Fonna; 2) Between 13 and 65 years; 3) Meet diagnostic criteria for prodromal syndrome SIPS criteria [11]; 4) Does not meet current or life-time criteria for any psychotic disorder; 5) The symptoms are not better accounted for by an axis I, axis II or substance use disorder with the exception of schizotypal personality disorder (the presence of any of these disorders in itself is not an automatic reason for exclusion); 6) Does not use any antipsychotic medication currently and have not used antipsychotic medication (regardless of dosage) for more than four weeks lifetime; 7) No known neurological or endocrine disorders that may have caused the presenting psychotic symptoms; 8) The patient is not mentally retarded with an IQ below 70; 9) The patient must be able to understand and speak Norwegian; 10) The patient must be able to understand and sign an informed consent or assent for minors’ document.

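### The 88.9% power is not derived from the reach and efficacy figures beside it; at the only reach figure given, power for the incidence comparison is far lower

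*Protocol article*

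**What the plan says.** The Power calculation section opens with a caveat: "There are no previous studies giving any clear suggestion of the number of high-risk individuals that can be recruited" from a catchment area of this kind. It then offers one indication, from Melbourne by personal communication, that "around 20% of first episode patients have been in contact with the PACE clinic". For efficacy it takes a "conservative estimate of a 20% transition rate over the first two years for a non-treated high-risk sample"; with active treatment the assumed figure is 10%.

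The next sentence moves to population counts: 150 first-episode cases a year among 750 000 people in Bergen and Østfold, and a reduction to 90 a year among 440 000 in Stavanger and Fonna. It claims 88.9% power. Alpha, sidedness and the number of years entering the test are not given there.

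The section on the psychosis incidence study names incidence in the participating areas as the main outcome, assessed over all study years. The only dates are in the section on prodromal inclusion and exclusion criteria ("Start of study inclusion is from March 1" of 2012, to 31 December 2016). They refer to recruitment of prodromal patients, not to incidence registration.

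**The concern.** The reach and efficacy figures together determine how far the programme can move population incidence, yet neither is carried into the counts on which the power rests. The reader is told that the trial is almost 90% likely to succeed, but not for what effect or at what reach.

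This affects how the result will be read. The abstract's discussion says negative results would suggest that the potential for psychosis is determined early in life. If treatment truly halved transition but the programme reached only a fifth of future cases, a non-significant result could be as likely as a significant one, or likelier. That inference would then be unsafe.

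**Working it through.** **Inputs from the protocol article**
- Control areas: 150 cases per year / 750 000 = 20.0 per 100 000.
- Intervention areas: population 440 000, so at the control rate 440 000 × 20.0 per 100 000 = 88 cases per year.
- Reach 20%; transition 20% untreated and 10% treated, so the relative risk reduction is 50%.
- Prodromal inclusion, 1 March 2012 to 31 December 2016: 58 months = 4.83 years.

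**Assumptions, not in the article**
- Two-sided 5%, with one-sided 5% as a check.
- Poisson counts with no variation between areas.
- Registration window of 4.83 years (equal to prodromal inclusion) or 6.83 years (adding the two-year follow-along of the last participant).

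**Step 1: the plan's own figure.** 90 / 440 000 = 20.5 per 100 000 against 20.0, a rate ratio of 1.02. The stated counts show no reduction, and 88.9% cannot be reproduced from them. With the test below, the chance of a significant result in either direction is about 5% in one year and 7% over 4.83 years. Figures near 88.9% appear only after substituting inputs. Reading the 90 against 750 000 (12 per 100 000, a 40% fall) gives about 91%, or 90% with continuity correction. Using 225 control cases (30 per 100 000, a 32% fall) gives about 88%.

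**Step 2: the effect implied by reach and efficacy.**
Rate ratio = 1 − reach × relative risk reduction = 1 − 0.20 × 0.50 = 0.90.
Incidence goes from 20 to 18 per 100 000; cases from 88 to 79.2 per year.

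**Step 3: power at that effect.** With C control and P intervention cases over the window, SE = √(1/C + 1/P), z = −ln(rate ratio)/SE, and two-sided power = Φ(z − 1.96) + Φ(−z − 1.96).

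| Window | C | P | SE | z | Two-sided 5% | One-sided 5% |
|---|---|---|---|---|---|---|
| 1 year | 150 | 79.2 | 0.139 | 0.76 | 12% | 19% |
| 4.83 years | 724.5 | 382.5 | 0.063 | 1.67 | 38% | 51% |
| 6.83 years | 1024.5 | 540.9 | 0.053 | 1.98 | 51% | 63% |

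Other test forms (pooled two-proportion test, continuity correction, event-count formula) give 10–12% for one year and 37–39% for 4.83 years, two-sided.

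**Step 4: background incidence.** The Rationale quotes 15 to 30 per 100 000 per year. For a 10% fall, two-sided power over that range is 30% to 53% at 4.83 years and 40% to 68% at 6.83 years. The most favourable combination tried (30 per 100 000, 6.83 years, one-sided) gives 78%.

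**Step 5: what 88.9% requires.** Two-sided over 4.83 years, the rate ratio must be about 0.81. At halved risk this means reach of (1 − 0.812)/0.50, about 38%.

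**Step 6: dependence on reach** (halved risk, two-sided 5%, 20 per 100 000).

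| Reach | Rate ratio | 4.83 years | 6.83 years |
|---|---|---|---|
| 20% | 0.90 | 38% | 51% |
| 30% | 0.85 | 71% | 85% |
| 40% | 0.80 | 92% | 98% |

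**The case against.** The strongest reply is that 20% is not the plan's reach. It comes from another service, is introduced after a statement that no clear recruitment figure exists, and the programme's information campaigns and detection teams are meant to bring more high-risk people into contact. This stands. A reader might infer that the plan's premises rule out the effect behind 88.9%, or that incidence can fall by 20% at most even if every reached case is prevented. The documents do not support either reading, because the 20% is nowhere adopted as a ceiling or a formal assumption. At 40% reach over 4.83 years, power exceeds 88.9%.

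A reader might also take the one-year 12% as the trial's power. That too goes beyond the text. The counts are annual inputs, and the incidence section already speaks of all study years, so the multi-year figures are the relevant ones. Their window is itself an assumption, since no registration dates are given.

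Finally, the stated counts fail on their own terms (Step 1), and correcting them will force a new power figure anyway. The two corrections belong together. Repairing the counts alone, however, would not say where the planned effect comes from. With 79 cases in place of 90, power is still well below 88.9%.

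This is not a matter that can be left to an analysis plan: the article prints a specific power, and the premises printed beside it do not yield it.

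**Conclusion.** The concern holds in this form: the 88.9% is unsupported by the reach and efficacy figures cited with it. At the only reach figure given, with transition halved, the implied fall in incidence is about 10%. Power is then about 38% over 4.83 years or 51% over 6.83 years two-sided, and 51% or 63% one-sided. No combination of window, sidedness or background incidence tried reaches 88.9% at 20% reach.

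The size of the shortfall is conditional on reach, on a 5% level and on the assumed window, none of which the article fixes. The calculations are also favourable to the trial. They assume the full effect from the first day, although transition is counted over two years; they treat everyone in contact as treated; and they ignore variation between only four areas.

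**What to change.** In the Power calculation section:
- State the assumed reach and the reason for it.
- Derive the planned rate ratio as 1 − reach × relative risk reduction.
- State alpha, sidedness and the incidence registration window.
- Replace 88.9% with the power over all registration years at 20%, 30% and 40% reach (38%, 71% and 92% under the two-sided 4.83-year assumptions), and give the detectable rate ratio (about 0.81 for 88.9% power).
- Correct the stated case counts in the same revision, so that the intervention-area count agrees with the derived rate ratio.

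The cost is one rewritten paragraph. The stated power becomes lower, or openly conditional on reach. Testing over all registration years needs no change of design, since the incidence section already points that way.

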### The psychosis incidence study

The main outcome of the intervention will be the incidence of psychotic disorders in the participating areas. This will be assessed using the same research diagnostic criteria; in all participating areas over all study years.

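### The stated 88.9% power does not follow from the case counts and populations printed with it, which contain no reduction in incidence

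*Protocol article*

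**What the plan says.** The Power calculation section describes two groups by catchment population and annual FEP count. The control group is "750 000 with predicted annually detection of 150 first-episode psychosis (FEP) (Bergen and Østfold"); the intervention group is "440 000 with annually predicted reduction to 90 FEP (Stavanger and Fonna) through prodromal detection and intervention". From these it concludes that "the study will have power of 88.9% to yield a statistically significant result".

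The same section gives two patient-level assumptions. One is a "conservative estimate of a 20% transition rate over the first two years for a non-treated high-risk sample and subsequently a 10% risk" in the treated group. The other, from experience in Melbourne, is that "around 20% of first episode patients have been in contact with the PACE clinic". It gives no number of high-risk individuals, no FEP count for Stavanger and Fonna without the programme, and no test, alpha or number of registration years.

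The section on the psychosis incidence study states: "The main outcome of the intervention will be the incidence of psychotic disorders in the participating areas". The power sentence, however, names a fall in transition rates as its target while its inputs are area counts of FEP.

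**The concern.** A power statement for an incidence comparison needs two different rates. The two printed here are practically the same, and the one described as reduced is marginally the higher. The claimed power therefore has no visible effect behind it.

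This is the only power justification in the article, and incidence is called the main outcome. The figure also affects how a null result will be read. The Discussion part of the abstract says in advance that negative results would point to early-life determination of psychosis. That inference is reasonable only if the study had a good chance of detecting a realistic effect, and the printed figures do not show that it had.

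**Working it through.** **Inputs.** From the Power calculation section: control areas 150 cases a year in 750 000; intervention areas 90 cases a year in 440 000; stated power 88.9%; reach about 20%; two-year transition risk 20% untreated and 10% treated. From the inclusion criteria: recruitment from March 2012 and "ending inclusion December 31^st^ 2016", that is 58 months or 58/12 = 4.83 years. Assumptions: alpha 5% two-sided, since the section says only "to yield a statistically significant result"; the number of registration years is varied, with the prodromal inclusion window as one value.

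**Step 1: rates.**
- Control: 150 / 7.5 = 20.0 per 100 000 per year.
- Intervention, after the assumed reduction: 90 / 4.4 = 20.45 per 100 000 per year.
- Rate ratio: 20.45 / 20.0 = 1.023.
- Cases expected in 440 000 at the control rate: 20.0 × 4.4 = 88.

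**Step 2: attempt to reproduce 88.9% from the printed inputs.** Wald test on the log rate ratio, with y years of data:
- ln(1.0227) = 0.0225; SE = √[1/(150y) + 1/(90y)].
- y = 1: SE = 0.133, z = 0.0225/0.133 = 0.169. Rejection probability = Φ(0.169 − 1.96) + Φ(−0.169 − 1.96) = 0.037 + 0.017 = 5.3%.
- y = 4.83: SE = 0.0607, z = 0.370. Rejection probability = 0.056 + 0.010 = 6.6%.
- The second term in each sum is the probability of a significant result favouring the programme: 1.7% and 1.0%. It falls with longer registration because the difference has the wrong sign.

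A pooled two-proportion z test, counting only the tail in which the printed difference lies, gives 3.7% for one year and 5.7% for five. The most generous variant tried (ten years, one-sided alpha 10%, again in the direction of the printed difference, which is the wrong one) gives 22.8%. The figure of 88.9% is not reproduced.

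**Step 3: other readings of the sentence** (two-proportion test, two-sided 5%).

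| Reading | Power |
|---|---|
| 20% vs 10% transition, taking 150 and 90 as group sizes | 53% |
| 150 vs 90 cases on equal denominators | 97.2% |
| 90 per 750 000 taken as the rate in the 440 000 | 91.2% |

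None of these gives 88.9% either.

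**Step 4: inputs that come close but are not printed** (same test).

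| Unstated input | Power |
|---|---|
| 54 cases a year in the intervention areas, one year | 88.9% |
| 63 cases a year, two years | 89.6% |
| 72 cases a year, five years | 88.6% |
| Before-after fall from 110 to 90 a year in 440 000, five years | 88.6% |
| Control rate 30 per 100 000 (225 cases, not 150), one year | 88.2% |

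The 54-case match depends on the test: the Wald test of step 2 gives 86.8% for the same count. Several quite different inputs land near the stated figure, so it cannot be traced back to one of them.

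**Step 5: illustration from the section's own assumptions.** If 20% of future cases are reached and their risk is halved (20% to 10%), the area reduction is 0.20 × 0.50 = 10%, and 88 × 0.90 = 79.2 cases a year, or 79.2 / 4.4 = 18.0 per 100 000. Two-sided power (pooled two-proportion test) is 11% for one year, 38% for 4.83 years and 40% for five. The article does not state this model; it only links its two patient-level figures to the area counts.

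**The case against.** The best defence is that the article is condensed. Test, alpha, registration years and the unreduced count may all stand in a fuller document, and a misprinted count, population or comparator would explain the sentence as well as a calculation that was never valid. This stands: the documents do not show that no valid calculation exists, and the absence of those details is not the criticism. It does not rescue the sentence, because the four numbers it does print are incompatible with the power attached to them under every standard variant tried.

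A reader might go further and infer that the design has no planned effect, so that its real chance of a significant result equals the type I error rate. The documents do not support that. A patient-level effect is stated (20% against 10% transition) together with an approximate reach. The study's real power depends on the true effect, the populations and the years of registration, none of which a misreported count alters. What is missing is a reduction in the printed area-level figures.

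A reader might also infer that the authors meant about 54 cases. That holds for one registration year and one particular test, whereas the incidence section says that assessment covers all study years. Step 4 shows other inputs that serve nearly as well, one of which keeps the printed 90.

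Finally, it could be argued that the power refers to transition in the high-risk sample, since the sentence mentions transition rates. But its groups are catchment populations with FEP counts, and no number of high-risk individuals is given. That ambiguity needs correcting too.

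**Conclusion.** The power statement is wrong as written. Its inputs are 20.0 and 20.45 per 100 000 per year, a rate ratio of 1.02 with no reduction, and they give a rejection probability of about 5% (one year) to 7% (4.83 years) rather than 88.9%. The rate comparison needs no assumption. The probabilities assume a two-sided 5% test and independent counts, but no alternative tried for alpha, sidedness or duration brings the printed inputs near the stated power.

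The 11% to 40% range is illustrative and rests on applying the Melbourne contact share as reach and the halved risk to everyone reached. It suggests that the problem may be more than a typing error, but does not establish it. Which printed number is wrong cannot be settled from the article.

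**What to change.** Rewrite the paragraph so that its figures agree:
- Reconcile the two counts, the two populations and the comparator (parallel areas or before-after).
- Say which outcome is powered: area incidence, or transition rate in the high-risk sample. If the latter, give the number of high-risk individuals.
- For area incidence, state the expected annual FEP in Stavanger and Fonna without the programme and with it, and how the second follows from the assumed reach and risk reduction.
- State the registration years, the test, alpha and sidedness, and the power that results.
- Withdraw 88.9% unless the inputs that produce it are given.

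The cost is a short recalculation and one rewritten paragraph. The stated power may turn out less favourable.

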### The psychosis incidence study

The main outcome of the intervention will be the incidence of psychotic disorders in the participating areas. This will be assessed using the same research diagnostic criteria; in all participating areas over all study years.

#### Incidence study inclusion criteria

1) The patient is listed in the national register and residing in the catchment areas of Stavanger, Fonna, Bergen, and Østfold; 2) Between 13 and 65 years; 3) Meet diagnostic criteria in DSM-IV for first-episode schizophrenia, schizophreniform disorder, schizoaffective disorder, delusional disorder, brief psychotic disorder, affective psychoses (Bipolar I disorder, Bipolar II disorder with psychotic symptoms, major depressive disorder with psychotic symptoms) or psychotic disorders NOS; 4) The patient is (or has recently been) active psychotic with symptoms of delusions, hallucinations, disturbed thinking, unsuitable/ bizarre behaviour which cannot clearly be explained by organic reasons. The symptoms must have lasted the whole day for several days or several times a week for several weeks, not limited to some brief moments corresponding to a score of at least 4 on one or more of the following positive and negative symptom scale (PANSS) [53] symptoms: P1 (delusions), P3 hallucinations), P5 (grandiose thinking), P6 (suspiciousness) and G9 (unusual thought content); 5) This is the first episode of the condition that is being adequately treated. i.e. the patient has not received antipsychotic treatment corresponding to 75% of a defined daily dosage for more than eight weeks (shorter if the symptoms remit); 6) There are no known neurological or endocrine disorders that may have caused the presenting psychotic symptoms; 7) The patient is not mentally retarded with an IQ below 70; 8) Able to understand and speak Norwegian; 9) Able to understand and sign informed consent/assent for minors’ document.

#### Assessments

The primary measure of the incidence study is psychotic caseness as ascertained by SCID (Kiddie SADS for adolescents who are 13–17 years old) assisted by the PANSS interview.

### Prodromal patient neuroimaging protocol

A fMRI protocol is set up for the prodromal study providing the possibility to study prodromal patients, and normal controls. The MR imaging is performed with a 1.5 tesla scanner (450 Discovery; GE Medical Systems) equipped with a standard head-and-spine (HNS) coil.

#### Structural images

A structural image is acquired after the functional imaging using a BRAVO sequence (GE Healthcare); a T1-weight 3D IR-prepared spoiled gradient echo-sequence with the following parameters: TR/TE/TI = 7.9 ms/3.1 ms/450 ms, FOV = 24 × 19.2 cm. Number of slices is 180 with a thickness of 1 mm. The in-plane sampling matrix is set to 240 × 192 resulting in an iso-tropic resolution of 1 mm. The total scan time is 6 min. 3 s.

#### Functional magnetic resonance imaging

##### Working memory task

Participants undergoes fMRI scanning while performing a numeric n-back WM task as used in previous studies [54-56]. The task contains two conditions: (1) in the “2-back” condition, participants are required to press a button when the number they see equales the number seen two numbers before; and (2) in the “0-back” condition, participants have to respond with a button press each time they see the number zero. Numbers between 0 and 9 is displayed for 500 ms with an intertrial interval of 900 ms. Each block consist of 22 stimuli containing three targets and is indicated by an instruction cue displayed for 2 seconds before each block. Stimulation blocks and resting periods alternates within the experiment with a total of six 2-back and six 0-back blocks. During resting periods, volunteers are instructed to fixate on a cross in the center of the screen.

MRI is performed using gradient-echo echo-planar imaging (TR, 2600 ms; TE, 35 ms; flip angle, 90°; matrix, 64 × 64; voxel size, 2 × 4 × 5 mm). The combination of a stimulus onset asynchrony of 1400 ms (500 ms stimulus duration; 900 ms intertrial interval) and a TR of 2600 ms resultes in 13 possible time points of stimulus presentation per TR. Across multiple stimulus presentations, this yields an effective sampling rate of 5 Hz. Twenty-four slices approximately parallel to the bicommissural plane (anterior commissure–posterior commissure plane) are collected, covering the whole brain. Twenty fMRI volumes are acquired per block: 12 during stimulation (2-back or 0-back) and eight during the resting period. Blocks are presented alternately three times in each of the two runs (A B A B A B). A total of 252 volumes are collected.

##### Resting state task

Subjects undergoes one 8 min scan during which they performed a resting-state, low-level baseline task (eyes open, visual fixation on a hair-cross-centered in the screen). MRI is performed using gradient-echo echo-planar imaging. The experiment consisted of a single session during which 180 BOLD sensitive EPI volumes are acquired with 25 axial slices (TR, 2500 ms; TE, 40 ms; flip angle, 90°, 5 mm slice thickness, no interslice gap, matrix, 64 × 64; field of view: 240 × 200 mm^2^; voxel size, 2 × 4 × 5 mm).

